## **3.2. Eligibility Criteria**

### ***3.2.1. Inclusion Criteria***

This study will adopt the following inclusion criteria (Appendix C):

1. Adults  $\geq 18$  years of age who are capable of giving informed consent
2. Patients meeting diagnostic criteria for major depressive disorder (MDD) without psychotic symptoms according to the Diagnostic and Statistical Manual of Mental Disorders – Fifth Edition (DSM-5) and currently experiencing a Major Depressive Episode (MDE) as confirmed at intake
3. A Montgomery-Asberg Depression Rating Scale (MADRS) score  $\geq 20$  at screening (moderate-to-severe MDE)
4. Failure of two or more adequate trials of antidepressant therapy of adequate dose and duration during the current episode as confirmed at intake
5. Undergoing clinical treatment at the Interventional Psychiatry Program at St. Michael's Hospital, Unity Health Toronto (SMH-UHT)
6. Ownership of a smartphone with Bluetooth capabilities (for participants using the Oura Ring)

### ***3.2.2. Exclusion Criteria***

This study will adopt the following exclusion criteria (Appendix C):

1. Subjects without internet access, as an internet connection is required for using the study platforms
2. Medication changes, aside from the treatment received through the IPP, one month (28 days) before screening, or during the entire duration of treatment (variable based on treatment arm).
3. Other exclusion criteria for this study will follow those from the clinical treatment the participant is receiving (Standard of care)

Participants without a smartphone with Bluetooth capabilities will not be eligible to receive the Oura Ring, as they must be able to download the Oura App (for data syncing and visualization).

However, these participants can still contribute data to the REDCap components of the study. Non-English-speaking individuals are excluded because it is necessary for participants to have the ability to communicate and understand study information, answer questions accurately and completely about the study, obtain informed consent, and complete self-report measures independently.

### **3.3. Withdrawal Criteria**

Participants are free to withdraw their consent and/or end their participation in the research study at any time without penalty or loss of benefits or treatment to which they are otherwise entitled. Participants may be withdrawn from the study by the study's doctor if they feel that it is in their best interest.

Participants may also be withdrawn if:

- The participant meets any exclusion criteria for this study
- The participant meets any exclusion criteria for the clinical treatment they are receiving within the IPP (either newly developed or not previously recognized)
- The participant stops receiving clinical treatment within the IPP
- Participant fails to adhere to study responsibilities
- They must be withdrawn from clinical treatment for any reason
- Anything, in the opinion of the investigator, that would place the participant at increased risk or preclude the participant's full compliance with or completion of the study.

If a participant withdraws from the study at any time, the reasons for withdrawal will be collected and documented as part of the feasibility outcome for this study. A time will be scheduled for the participant to return the Oura Ring (if applicable). Data collected up until the point of withdrawal will be used for analyses.

### **3.4. Concomitant Medications**

Participation in the study will not alter the standard of care, including any required changes to treatment regimens. Medications will be monitored on a regular basis and may be restricted as part of the standard of care for their respective clinical treatment. Participants will be required to

continue with their respective approved treatment for MDD throughout the study. Before the intervention, investigators will analyze all medications taken by participants on a regular basis. No medication changes, aside from the treatment received through the IPP, are allowed one month (28 days) before screening, or during the entire duration of treatment (variable based on treatment arm) and follow-up (14 days) due to the probable impact on brain activity and psychiatric symptoms. Participation in the study will not alter the standard of care, including any required changes to treatment regimens. If any changes to concomitant psychotropic medications are required as per the patient's standard of care, the participant will be withdrawn from the study.

### **3.5. Concomitant Care**

Regular psychiatric care will be provided by the participant's primary responsible physician without restriction.

### **3.6. Interventions**

Details on the active (self-report clinical scales) and passive (wearable device) digital interventions are described below.

All data collection will be de-identified, such that participants will be assigned a unique identification (ID) number and de-identified dummy email address. The study ID will be entered into the REDCap platform and used for all CRFs, in lieu of personally identifying information. The de-identified email address and associated password will be used to set-up participants' wearable app accounts and will be used for email forwarding (to participants' personal email addresses) to ensure participants remain de-identified on the Oura platform.

The Study Coordinator will manage recruitment, informed consent, and liaise with the clinical team throughout the course of treatment. The clinical team will enter patient-participant data directly into REDCap (based on intake and CRFs collected as part of clinical care in the IPP) so as to simply observe the clinical process (not intervene) and minimize data loss. A member of the research team (engagement specialist) will monitor wearable data compliance on a weekly basis; if a participant's Oura data is missing for 3 or more days (over the past 7 days), the

clinical team will be notified so they can connect with participants and refer them to the research team to troubleshoot any technical issues as needed. The clinical team will provide regular reminders at in-person treatment sessions to charge their wearable device and regularly synchronize, and visualize, their passive data in the smartphone app.

### **3.6.1. REDCap**

Participants will complete mental health related self-report questionnaires as part of their clinical care; the specific scales and frequency to be completed will be dependent on IPP clinic process and will vary across treatment arms (e.g., rTMS patients complete the GAD-7 and PHQ-9 for each treatment session, IVK patients complete the GAD-7 and MADRS at each treatment session). The clinical team will enter patient-participants' questionnaire responses directly into the REDCap platform after the treatment session (Appendix A).

### **3.6.2. Oura Ring Wearable Device**

We anticipate approximately 60 Oura Rings will be available for participants in this study. Participants who have a smartphone compatible with the Oura App and understand the requirement of returning the wearable device at the end of the study will be eligible for receiving the Oura Ring. Depending on availability, participants will be offered a commercially available wearable device to use for the duration of the study to collect passive data that is relevant to mental health and well-being such as physiological data, sleep and activity patterns. The Oura Ring is a wearable device that can be used without obstructing one's daily life. Detailed information on the features to be collected by the Oura Ring are summarized in Section 3.8.4.2.2 (Table 1). The Oura Ring device has its own mobile app for data visualization and self-management.

The Oura Ring has been successfully used in previous research studies to provide information on the behaviour of body systems (e.g., autonomic nervous system, sleep/circadian rhythm) in real-time through accurate measures of physiological parameters, sleep and activity. A recent study using the Oura Ring reported significant associations between depressive symptoms and sleep features, with the combined use of the ring, mobile app, and self-reported mood providing the strongest prediction of depression. In the proposed study, we will use Oura Ring

to continuously collect activity, sleep, and physiological signals for retrospective modeling and integration with active (clinical assessment) data to more precisely monitor a participant's activity, behaviour, and wellbeing as compared to either of these platforms alone. The description of the physiological data to be collected by the Oura Ring is provided below as follows:

1. Sleep information: Oura Ring performs sleep analysis and stores a set of measurement parameters that summarize each period. The ring calculates the sleep period specific parameters within four hours from the period end, but sleep analysis is always triggered when you open the application. These parameters include bedtime, total duration, awake, light, Rapid Eye Movement (REM), and deep sleep durations, and also heart rate, breathing, temperature changes during sleep.
2. Activity information: Activity summary contains daily activity summary values and detailed activity levels. Activity levels are expressed in metabolic equivalent of task minutes (MET mins). Oura tracks activity based on the movement and presents the activity score based on duration of low, medium, and high activity levels. The movement is also used for step count and to estimate calories.
3. Readiness information: Readiness score is interpreted from sleep, activity, resting heart rate, heart rate variability, recovery index and temperature scores. A Readiness Score above 85% indicates that you're well recovered. A score below 70% usually means that an essential Readiness Contributor, such as body temperature or previous night's sleep, falls outside your normal range, or clearly differs from recommended, science-based values.

The wearable device privacy policy will be made available for all potential users to read. Data collection via the Oura Ring for selected participants will start approximately three weeks before the clinical treatment begins, continuing throughout the intervention and ending on the last day of treatment. Oura Rings will be returned to the clinical team at the end of their last treatment session.

Data collected via Oura will be de-identified using a de-identified study ID and email address which will be used to login to their account on the Oura app. This will ensure that participants are de-identified on this third-party platform (Oura).

A member of the research team will monitor data compliance on a weekly basis. If participants have Oura data that are missing for 3 or more days over the past 7 days, the clinical team will be notified so they can follow up with participants. Participants will be referred to the research team as needed to troubleshoot any technical issues.

### 3.7. Outcomes

All outcomes will be assessed at different stages of the study. Please refer to the study's schedule, section 3.8.1, for a detailed depiction of the nature and frequency of all assessments.

|                   |                                                                                                                                                                                                                                                                                                                                                                                                                                                                                                                                                                                              |
|-------------------|----------------------------------------------------------------------------------------------------------------------------------------------------------------------------------------------------------------------------------------------------------------------------------------------------------------------------------------------------------------------------------------------------------------------------------------------------------------------------------------------------------------------------------------------------------------------------------------------|
| Primary Outcome:  | 
Feasibility of REDCap and the Oura Ring will be measured by:
 
 
1) Number of recruitments (minimum threshold: 6-7 participants/month)
 
2) Recruitment rates (proportion of recruited participants over the total number of patients invited for this study)
 
3) Dropout rate (maximum threshold: 30%) and reasons for dropping out
 
4) Data completion rates (minimum threshold: 70%)
 
 
Data will be compared among responders versus non-responders as well those who do and do not relapse and/or remit
 |
| Secondary Outcome | 
Clinical outcomes will be measured by:
 
 
a) Quantifying changes in active (self-report) and passive (physiological) data over time
 
b) Predicting treatment response , remission, and relapse based on active (self-report) and passive (physiological) data .
 
                                                                                                                                                                                                                                                                |

|  |                                                                                                       |
|--|-------------------------------------------------------------------------------------------------------|
|  | c) Constructing personalized digital phenotype profiles (pDPPs) based on wearable and web-based data. |
|--|-------------------------------------------------------------------------------------------------------|

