### **3. METHODS**

#### **3.1. Study Design**

This observational study with retrospective data analysis will assess the feasibility of multimodal digital platforms to collect active (self-report) and passive (wearable biometrics) data and enable self-monitoring of adult patients receiving clinical treatment for TRD. Specifically, we will assess the feasibility of using a web-based electronic data capture platform (REDCap) and a wearable device (Oura Ring) to collect active and passive data, respectively, in tandem with neuropsychiatric treatment for TRD in the IPP. The overall duration of this study is three years. However, each participant will only be enrolled in this study for the duration of their clinical treatment in the IPP. All participants will begin participation during the first study visit (known as the Screening and Baseline Visit), which will take place upon scheduling of the first treatment session. For participants receiving the Oura Ring, the Screening and Baseline Visit will occur in-person (so they can obtain an Oura Ring) and will take place approximately three weeks before the first treatment session, to establish baseline parameters measured by the Oura Ring. For participants not receiving the Oura Ring, their clinical treatment can begin after the

Screening and Baseline Visit (usually ~0-3 weeks after), therefore, some participants may complete these measures at their first treatment session .

Following REB approval, 200 patients aged 18 years or older will be recruited over 33 months and will have their self-report assessments (GAD-7 and, if applicable, PHQ-9) entered on the REDCap platform for use in research (see Appendix A). Depending on the availability of Oura Ring devices, a subset of participants will also be offered the opportunity to use an Oura Ring, which is a wearable device that will collect data on sleep, activity, and physiological data in near real-time during their participation in this study. We estimate that approximately 60 Oura Ring devices will be available for participants to use. Potential participants will be adults with TRD enrolled for clinical treatment at the IPP at St. Michael’s Hospital, Unity Health Toronto (SMH-UHT). Participants will receive one of the clinical treatments at the IPP according to clinical protocols and standard of care (Figure 1). The details of the study design are summarized in Figure 2.

[figure not shown]

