## **5. DATA ANALYSIS METHODS**

### **5.1 Statistical Analysis**

We will assess the feasibility of digital interventions using descriptive statistics with counts and proportions for categorical data and means and standard deviations (parametric) or median and interquartile range (non-parametric), as appropriate, for continuous data. The proportion lost to follow-up will be estimated along with a 95% confidence interval. The upper 95% confidence limit should not exceed 20% to proceed. The proportion compliant with the protocol, including treatment compliance as well as study completion and complete data on clinical outcomes (i.e., the per-protocol group) will be estimated with a 95% confidence interval. For validity, this

should be fairly high so that the lower 95% confidence limit is  $> 80\%$ . Group- (*t*-tests, ANOVA, ANCOVA, correlation, regression) and individual- (multilevel modeling) level biostatistics will be used to identify and quantify changes in active (anxiety and depression symptoms) and passive (biometrics) data across treatment arms and over time.

Machine learning and advanced analytics (e.g., dimensionality reduction, statistical relevance or multi-view bi-clustering) will also be used to fuse the passive physiological data with the active questionnaire data. More specifically, passive data is effective at identifying behaviours and trends in activity but is poor in measuring people's internal states, motivation, and attitude, whereas active data is the opposite. Developing a methodology for integrating the two data sources can mitigate their respective weaknesses. The passive physiological data will be fused with the active data collected by the REDCap platform. The motivation to fuse active and passive data includes the cross-validation and improvement of measurements, the explanation of human behaviour, and novel opportunities to improve causal inference in experimental settings.

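### Section 3.7 tolerates 30% dropout, while Section 5.1 says to proceed only if the upper 95% limit for loss to follow-up is at most 20%; the protocol neither separates the two terms nor says which rule governs

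*Protocol*

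**What the plan says.** Protocol Section 3.7 (Outcomes) defines the primary outcome, feasibility, by four measures. Three carry a cut-off:

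- "Number of recruitments (minimum threshold: 6-7 participants/month"), a minimum given as a range;
- "Dropout rate (maximum threshold: 30%) and reasons for dropping out";
- "Data completion rates (minimum threshold: 70" per cent).

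No confidence limit is mentioned, so the natural reading is that the observed value is compared with the cut-off.

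Section 5.1 (Statistical Analysis), in its paragraph on assessing feasibility, uses other quantities and cut-offs. On loss: "The proportion lost to follow-up will be estimated along with a 95% confidence interval", followed by "The upper 95% confidence limit should not exceed 20% to proceed". It then turns to the proportion compliant with the protocol, "including treatment compliance as well as study completion and complete data on clinical outcomes (i.e., the per-protocol group"). For validity, this "should be fairly high so that the lower 95% confidence limit is" above 80%.

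Section 5.1 does not mention the 30% or 70% thresholds, and 3.7 does not mention the 20% or 80% limits. On size and pace, Section 3.1 says that "200 patients aged 18 years or older will be recruited over 33 months".

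**The concern.** Feasibility is the primary aim, and the loss sentence in 5.1 is worded as a condition for going on, not as a description. Two sections therefore appear to judge the same kind of event against different limits, one on the observed proportion and one on a confidence limit, with no order of precedence. If the observed dropout falls between the two limits, the study can be called feasible by citing 3.7 or not feasible by citing 5.1, and that choice could be made after the data are seen. A statistical analysis plan could not settle this without overriding one of the two protocol sections.

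**Working it through.** **Inputs.** n = 200 (Section 3.1); dropout cut-off 30% (3.7); upper 95% limit of at most 20% for loss, and lower 95% limit above 80% for the per-protocol proportion (5.1); 33 months and 6-7 per month (3.1, 3.7). The protocol names no interval method, so three common two-sided ones are shown. With p = x/n and z = 1.96:

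- Wald: p ± z·√(p(1−p)/n)
- Wilson: [p + z²/(2n) ± z·√(p(1−p)/n + z²/(4n²))] / (1 + z²/n)
- Exact (Clopper-Pearson): the upper limit is the 0.975 quantile of Beta(x+1, n−x)

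**Step 1: what 3.7 allows.** 0.30 × 200 = 60 dropouts.

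**Step 2: what 5.1 allows.** Upper 95% limits at n = 200:

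| Losses | Observed | Wald | Wilson | Exact |
|---|---|---|---|---|
| 28 | 14.0% | 18.8% | 19.5% | 19.6% |
| 29 | 14.5% | 19.4% | 20.05% | 20.2% |
| 30 | 15.0% | 19.95% | 20.6% | 20.7% |
| 31 | 15.5% | 20.5% | 21.2% | 21.3% |
| 40 | 20.0% | 25.5% | 26.1% | 26.2% |
| 60 | 30.0% | 36.4% | 36.7% | 36.9% |

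Example (Wald, 30 losses): 0.15 + 1.96 × √(0.15 × 0.85/200) = 0.1995. The largest count that passes is 28 (Wilson, exact) or 30 (Wald). Read as one-sided 95% limits, it becomes 30 (Wilson, exact) or 31 (Wald), which changes little.

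**Step 3: zone of disagreement.** If dropout and loss are the same quantity, counts from 29 (Wald 31) to 60 pass 3.7 and fail 5.1. Reading the 30% as an upper confidence limit does not remove the gap: that would allow 47 (Wilson, exact) or 48 (Wald), against 28 or 30.

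**Step 4: chance of each verdict.** With X ~ Binomial(200, π):

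| True dropout π | 3.7: P(X ≤ 60) | 5.1: P(X ≤ 28) | 5.1 by Wald: P(X ≤ 30) |
|---|---|---|---|
| 15% | 1.00 | 0.39 | 0.55 |
| 20% | 1.00 | 0.02 | 0.04 |
| 25% | 0.95 | 0.00 | 0.00 |

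**Step 5: if loss to follow-up is narrower than dropout.** The per-protocol proportion requires study completion. The lower limit first exceeds 80% at 172/200 (Wilson 80.5%, exact 80.4%; at 171 they are 79.95% and 79.8%) or at 170/200 by Wald (80.05%; at 169 it is 79.5%). So at most 28 (Wald 30) participants can fall outside the group for any reason. With 60 dropouts, at most 140/200 = 70% can be per-protocol, and the lower limit for 140/200 is 63.1% to 63.7%.

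**Step 6: recruitment.** 200/33 = 6.06 per month. Six per month gives 6 × 33 = 198 and seven gives 7 × 33 = 231. Recruiting exactly to plan passes a minimum of 6 and fails a minimum of 7.

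**The case against.** The strongest reply is that dropout and loss to follow-up may be different things. Sections 3.3 and 3.4 provide for withdrawal by the study, for instance after a medication change or when treatment in the programme stops. Such participants could count as dropouts without being lost. Section 3.4 also refers to a 14-day follow-up, and the table of contents lists a follow-up section, although the body contains no such section and the schedule shows no visit after treatment. A reader might infer that loss to follow-up can only mean dropout; the document does not establish that. If loss is a subset, a study with 20% dropout and 8% lost could pass both rules. This objection stands as far as the loss sentence goes, and the both-pass-and-fail zone is conditional on the terms being the same. It does not rescue the plan as a whole, because the per-protocol aim counts study completion however loss is defined.

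Other tempting readings go too far:

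- **That 70% completion conflicts with the 80% limit.** Data completion covers the REDCap and ring data. The per-protocol proportion counts participants who complied with treatment, completed the study and have full clinical outcomes. These are different measures, and 70% of the first does not preclude meeting the second.
- **That 5.1 contains two go/no-go rules.** Only the loss sentence is a condition for proceeding. The per-protocol limit is a validity aim.
- **That the recruitment threshold contradicts the plan.** The planned 6.06 per month lies within the stated range, and 5.1 sets no recruitment limit. The fault is only that a minimum is given as a range.
- **That the ring subset has a firm limit of its own.** At n = 60 the 5.1 rule would allow 5 losses (Wald 7). But 60 is a device count, Section 3.8.5.2.2 has rings reissued to new participants, and 5.1 does not say that its limits apply to ring users.

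It is also fair to say that this is an observational pilot. The conflict affects the feasibility verdict, not data collection or care.

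**Conclusion.** The concern holds for dropout. If dropout and loss to follow-up are the same quantity, observed rates from 14.5% (Wald 15.5%) to 30% at n = 200 satisfy 3.7 and fail 5.1, and for true rates of 20% to 25% the two rules will almost always disagree. If loss is the narrower term, tolerating 30% dropout remains incompatible with the per-protocol aim in 5.1. The exact counts assume that all 200 participants form the denominator and that 3.7 compares the observed proportion; the conflict itself does not depend on the interval method or on whether the limit is one- or two-sided. The recruitment range is a secondary ambiguity. Because this is the decision rule for the primary outcome, it should be settled before data are reviewed.

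**What to change.** Put one set of progression criteria in 3.7 and have 5.1 refer to it. Give one definition covering dropout and loss to follow-up. State whether the observed proportion or its 95% confidence limit is compared with the cut-off, the interval method, and the denominator (all participants or ring users). The sponsor then chooses between:

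- **(a)** observed dropout of at most 30%, with its 95% interval reported and the 20% and 80% limits in 5.1 relabelled as descriptive; or
- **(b)** the confidence-limit rule of 5.1, with the 30% in 3.7 replaced by the observed proportion that it implies: about 14% at n = 200, recomputed for the actual n, since the Trial Summary sets no recruitment limit.

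Keep data completion and the per-protocol proportion as separate measures. State the recruitment minimum as one figure that the target meets, for example 6 per month or 200 in 33 months. A rounded 6.1 per month would not do as a minimum: 6.1 × 33 = 201.3, which the planned 200 misses.

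The cost is protocol wording and an ethics board amendment under Section 6.2; no procedure or sample size changes. Option (a) gives up assurance about the true dropout rate. Option (b) is demanding: a study with a true dropout of 15% would pass with probability of only 0.39 (Wald 0.55).

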The last treatment arm in the IPP comprises ECT, which is reserved for patients who fail to respond to rTMS and IVK. ECT is a safe and effective treatment for several mental health conditions, including depression, bipolar disorder, and schizophrenia, which have not improved from other treatments. Also, it may be considered the most effective treatment modality in psychiatry and with robust anti-suicidal effects. ECT involves administering a brief, controlled electrical current between two electrodes applied on the surface of the scalp or temple. The current stimulates a specific part of the brain and causes a small, controlled seizure which lasts between 15 and 90 seconds, and the whole procedure is performed under general anesthesia.

In this study, we will be assessing the uptake and feasibility of using a web-based platform (Research Electronic Data Capture – REDCap) and a wearable device (Oura Ring) to collect data from adults receiving treatment for TRD, using the following metrics: number of recruitments, recruitment rates, dropout rates and reasons for dropping out, and data completion rates. In addition, by collecting dynamic digital (active and passive) data, we will be able to analyze this data with respect to treatment response, remission, and relapse rates for each treatment arm. Treatment response is defined as a 50% or greater decrease in clinical symptoms (as captured by clinical assessments or self-report scales: MADRS, GAD-7, and PHQ-9); remission is defined as clinical assessment scores below the clinical threshold (e.g., MADRS  $\leq 10$ ); and relapse is characterized by the recurrence of symptoms after a patient has achieved remission (e.g., MADRS  $\geq 20$  after initial remission).

There are concerns that the use of digital platforms may affect the therapeutic relationship, yet there is a paucity of studies exploring this impact. A prior study focused on the effects of Information & Communication Technologies (ICT) in two culturally distinct countries, and the authors reported that the increased deployment of ICT facilitated patient empowerment.

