### 3.8.5.2. Digital Intervention Data Collection

#### 3.8.5.2.1. Active Data – Self-Report Questionnaires via REDCap

For active data collection, a member of the clinical team will enter patient-participants' self-report questionnaire and (if applicable) clinical assessment responses directly into the REDCap platform at the end of each study visit and treatment session (Appendix A). Active data will be used in combination with passive data – activity, sleep, and physiological data – for correlation and prediction of the clinical landmarks of response, remission, and depressive relapse.

As per IPP clinic process, participants will complete the following assessments on each treatment session day (approximately 10 - 30 minutes):

1. Anxiety: Generalized Anxiety Disorder - 7-item scale (GAD-7)
2. Depression: Patient Health Questionnaire- 9-item scale (PHQ-9) or Montgomery-Asberg Depression Rating Scale (MADRS)

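### Read in place, the primary-outcome comparison by response, remission or relapse sets dropout against groups that a participant can enter only by staying enrolled, so responders' dropout is biased downward

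*Protocol*

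**What the plan says.** Protocol section 3.7 measures feasibility, the primary outcome, in four ways: number recruited, recruitment rate, "Dropout rate (maximum threshold: 30%) and reasons for dropping out", and data completion with a 70% minimum. The same table cell then ends with "Data will be compared among responders versus non-responders as well those who do and do not relapse and/or remit".

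The groups in that sentence are states reached after baseline. In section 2.1, "Treatment response is defined as a 50% or greater decrease in clinical symptoms", remission is a score below a clinical threshold, and "relapse is characterized by the recurrence of symptoms after a patient has achieved remission". Section 2.1 ties none of these to a time point.

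The scores come from treatment visits: under section 3.8.5.2.1, "participants will complete the following assessments on each treatment session day". Observation ends with treatment, since by section 3.1 "each participant will only be enrolled in this study for the duration of their clinical treatment in the IPP". For people who leave early, section 3.3 says "Data collected up until the point of withdrawal will be used for analyses".

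**The concern.** To be counted as a responder, a participant must still be enrolled when a qualifying score is recorded. A remitter must do the same. A relapser must stay through remission and then through a later high score. Remaining enrolled is also what the dropout rate measures. The grouping variable therefore contains part of the outcome, which is immortal-time bias. Someone who leaves after one or two sessions has had little chance to enter any of these groups.

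Data completion has the same problem if its denominator is the planned number of sessions or days, because early leavers then score low. It largely escapes if the denominator is the time actually enrolled.

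At stake is a table under the primary outcome that could show the digital suite as better tolerated by patients who respond, when the pattern comes from how the groups were formed. Section 7 presents the study as groundwork for larger ones, so such a table could carry weight.

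**Working it through.** The protocol gives no figure for dropout by response group, so there is nothing to reproduce. The check asks what the comparison would show if response and dropout were unrelated.

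**Inputs**
- K = 6 sessions: section 2.1, ketamine twice weekly for three weeks.
- D = 30% overall dropout: the maximum in section 3.7, used as a scenario and not as an expected rate.
- R = 50% responding if nobody left: an assumption.
- Constant and independent hazards of dropout and first response: an assumption.
- Responder = response seen while enrolled; everyone else = non-responder. The second half of this rule is an assumption.

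**Per-session hazards**
- Dropout: h = 1 − 0.70^(1/6) = 0.0577
- First response: r = 1 − 0.50^(1/6) = 0.1091

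**Case A: dropout acts before each session's score.** The probability of a first response at session k while enrolled is p = (1 − h)^k (1 − r)^(k−1) r. The probability of leaving afterwards is q = 1 − (1 − h)^(6−k).

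| k | p | q | p × q |
|---|---|---|---|
| 1 | 0.1028 | 0.2571 | 0.0264 |
| 2 | 0.0863 | 0.2116 | 0.0183 |
| 3 | 0.0724 | 0.1633 | 0.0118 |
| 4 | 0.0608 | 0.1121 | 0.0068 |
| 5 | 0.0511 | 0.0577 | 0.0029 |
| 6 | 0.0429 | 0 | 0 |
| Sum | 0.4163 | | 0.0663 (before rounding of rows) |

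- Dropout in responders: 0.0663 / 0.4163 = 15.9%
- Dropout in non-responders: (0.30 − 0.0663) / (1 − 0.4163) = 40.0%

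A simulation of 2 million participants gave 15.9% and 40.1%.

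**Case B: each score is recorded before any dropout.** Here p = (1 − h)^(k−1) (1 − r)^(k−1) r and q = 1 − (1 − h)^(7−k). The sums are 0.4418 and 0.0918.
- Responders: 0.0918 / 0.4418 = 20.8%
- Non-responders: (0.30 − 0.0918) / (1 − 0.4418) = 37.3%

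**Sensitivity (case A timing).** Over 6, 20 or 30 sessions, 10–30% dropout and 30–70% response, the spurious gap runs from 6.6 to 31.6 points. Only the six sessions and the 30% ceiling come from the protocol.

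**Other ways to classify people who leave**
- Response judged at the end of treatment, leavers counted as non-responders: 0% in responders by definition, against 0.30 / (1 − 0.70 × 0.50) = 46.2%.
- Leavers who had not yet responded are excluded: non-responder dropout becomes 0% by definition, against 15.9% in responders (case A).
- Everyone without a final score is excluded: 0% in both groups, and nothing is left to compare.

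**Landmark check.** Classify response at session 3 among those still enrolled, and count only later dropout. The expected rate in both groups is 1 − 0.70^(3/6) = 16.3% (simulated: 16.3% and 16.4%). The artefact is gone. By the same formula 16.3% of participants leave before session 3, which is 0.163 / 0.30 = 54% of all dropouts, or about 33 of 60 among 200 participants.

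**The case against.** The strongest reply is that the sentence does not name dropout. Section 2.1 lists the feasibility metrics and then, separately, speaks of analysing the active and passive data in relation to response, remission and relapse. Two of the four measures, number recruited and recruitment rate, cannot be split by response at all. This stands as a real ambiguity. Against it, the sentence sits in the primary cell under dropout and data completion, while change in and prediction from the active and passive data have their own secondary cell. The natural reading in place includes dropout, and on the other reading the sentence is in the wrong cell.

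A reader might infer that the protocol classes early leavers as non-responders. It does not; section 3.3 says only that their data are used. An analysis plan may set the rule. But the alternatives worked through above either distort the comparison in another way or empty it, so the difficulty lies in the stated comparison and not in a missing detail.

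A reader might also infer that the feasibility verdict itself is biased. The documents do not support that. The limits in section 3.7 are not stated by response group, the confidence-limit criteria in section 5.1 concern overall proportions, and no test of dropout by response is specified.

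Finally, it is tempting to say that variable course length makes the bias worse. That was not shown. No calculation mixed course lengths, and in case A the gap is slightly smaller with 20 sessions (17.7% against 39.1%) than with six.

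**Conclusion.** The point holds in a conditional form. If the comparison in section 3.7 covers dropout, as its placement indicates, responders' dropout is biased downward with no true association. With early leavers counted as non-responders, the illustration gives about 16–21% against 37–40%, depending on whether scores precede dropout.

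Those sizes rest on the assumed 50% response rate, constant independent hazards and 30% taken as the actual dropout. Remission and relapse were not calculated. They follow by the same reasoning, and relapse requires the longest stay. The observed direction could reverse if responders left about 2.6 to 3 times faster once they had responded (R = 50%, D = 30%), but the downward push on their rate would remain. Data completion is affected only if its denominator is planned rather than enrolled time. The overall thresholds stand as they are.

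**What to change.** In section 3.7, state that dropout and data completion in all enrolled participants are the primary feasibility result, and do not compare whole-study dropout by eventual response, remission or relapse.

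If a comparison by response or remission is wanted, label it descriptive and use one of two forms, with matching wording in section 5.1:
- Response or remission as a time-varying state in a time-to-dropout analysis. This keeps every dropout.
- An early fixed landmark for each treatment, among those still enrolled, counting only later dropout. Earlier leavers are listed as 'outcome not determined'.

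In either case, express data completion per expected session or day while enrolled.

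If 'Data' was meant to be only the active and passive data, say so and move the sentence to the secondary outcome.

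The cost is wording and a little more analysis, with no new data. The landmark has a real price: with a mid-course landmark, about half of the dropouts (54% in the illustration) leave the between-group comparison. The time-varying model avoids that loss.
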